## Objectives

The specific objectives of this trial are:

• To compare the efficacy and safety of a continuous infusion of furosemide versus placebo titrated to the physiology parameter of urine output in early AKI on the primary outcome of progression in severity of kidney injury from early AKI.

• To evaluate the impact of furosemide versus placebo on key secondary endpoints including: fluid balance; electrolyte and acid-base balance; the need for RRT; total duration of AKI; the rate of renal recovery; and mortality.

• To evaluate the impact of furosemide versus placebo on the tertiary endpoint of differences, trajectory and prognostic value of novel serum and urine biomarkers for AKI.

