### Statistical Analysis

The primary analysis will evaluate the proportion of critically ill patients with early AKI that have progression in kidney injury by having received furosemide or placebo. Analysis will be intention-to-treat.

The secondary analysis will evaluate for differences between furosemide and placebo in cumulative fluid balance and in the largest changes to serum potassium, serum magnesium, serum pH and serum bicarbonate levels, defined as difference from enrollment to lowest documented level during study infusion. In addition, this secondary analysis will evaluate for differences in the need for RRT, duration of AKI, rate of renal recovery and hospital mortality.

Descriptive statistics, boxplots and histograms will be used to analyze individual baseline variables by having received furosemide or placebo. Normally or near normally distributed, non-correlated variables will be reported as means with standard deviations (SD) and compared using the appropriate Student's t test. Non-normally distributed, non-correlated continuous data will be reported as medians with inter-quartile ranges (IQR) and compared using the Mann Whitney U test. Non-correlated categorical data, including the primary outcome, and need for RRT, renal recovery and hospital mortality, will be reported as proportions and compared using Fisher's Exact Test. If necessary, multi-variable logistic or linear regression will be used to control for potential confounding from imbalances in baseline characteristics after randomization.

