The tertiary analysis will evaluate for differences between furosemide and placebo in the change of novel serum and urine biomarkers for AKI, defined by absolute levels and relative to baseline (enrollment) at 12 hours, 24 hours and at the time of initiation of RRT, renal recovery or ICU discharge. All samples will remain blinded during processing, storage and analysis. Normally distributed correlated data will be analyzed by the repeated measures ANOVA. Non-normally distributed correlated data will be analyzed by the Friedman test. Correlated categorical data will analyzed by generalized estimating equations. The diagnostic and predictive characteristics of absolute values and relative changes in novel serum and urine biomarkers for progression of AKI as well as need for RRT will be evaluated by 2 x 2 tables and construction of receiver operator characteristic curves. A p-value of < 0.05 will be considered significant. All statistical tests will be two-sided.

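### The Friedman test named for non-normal serial biomarkers has no treatment-arm term, so it cannot answer the tertiary furosemide-versus-placebo question

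*Protocol article*

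**What the plan says.** The Objectives section compares furosemide with placebo on the "tertiary endpoint of differences, trajectory and prognostic value of novel serum and urine biomarkers for AKI". The Statistical Analysis section repeats the between-arm aim: "The tertiary analysis will evaluate for differences between furosemide and placebo in the change of novel serum and urine biomarkers for AKI". It defines the change by absolute levels and by values "relative to baseline (enrollment) at 12 hours, 24 hours and at the time of initiation of RRT, renal recovery or ICU discharge".

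The same paragraph then assigns methods by type of data. For continuous markers it says "Normally distributed correlated data will be analyzed by the repeated measures ANOVA", followed by "Non-normally distributed correlated data will be analyzed by the Friedman test". Correlated categorical data go to generalized estimating equations. The only nonparametric two-group test in the article comes one paragraph earlier and is limited to other data: "Non-normally distributed, non-correlated continuous data will be reported as medians with inter-quartile ranges (IQR) and compared using the Mann Whitney U test".

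Data Collection lists seven markers: cystatin C and NGAL, each in serum and urine, and urine IL-18, KIM-1 and L-FABP. Samples are taken at baseline, 12 h, 24 h and daily thereafter.

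**The concern.** The question is between arms, but the method named for one branch of the data works only within patients. Repeated values of a marker in one patient are correlated, so on a plain reading any marker that is not normally distributed goes to the Friedman test. A significant result there shows that the marker changed over time. It does not show that furosemide changed it.

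There are two risks. A time course common to both arms could be read as a drug effect, and a real arm difference could be missed. The Discussion says the trial is meant to help design a phase III trial, so a misread biomarker result could be carried forward.

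**Working it through.** **Figures in the plan.** The article gives no figure for the biomarker analysis. Its one calculation is for the primary outcome, 60% against 40% progression with 80% power at two-sided alpha 0.05. It reproduces at 107 per arm with a continuity correction, 2 × 107 = 214, and is not in dispute. The final 216 gives 216 / 2 = 108 per arm, assuming equal allocation.

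**Structure of the test.** With N patients, k times and R_j the sum over patients of the within-patient ranks at time j:

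Q = [12 / (N k (k + 1))] × Σ R_j² − 3 N (k + 1), referred to chi-square on k − 1 degrees of freedom.

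For N = 216 and k = 3:
- 12 / (216 × 3 × 4) = 1/216
- 3 × 216 × 4 = 2592
- so Q = Σ R_j² / 216 − 2592, on 2 degrees of freedom.

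The arm label appears nowhere. In one simulated data set, reordering the 216 patients left Q at 4.7037 (p = 0.0952). This needs no assumption about effects or variances.

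**What that means in practice.** All inputs below are assumptions, because the article gives no biomarker means or variances: 108 per arm, log marker at 0, 12 and 24 h, between-patient SD 1.0, within-patient SD 0.7, linear time courses, and 1,500 simulated trials per scenario. The comparison is a baseline-adjusted arm test at 24 h.

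| True state | Pooled Friedman rejects | Arm test rejects |
|---|---|---|
| Both arms fall by 0.2 to 0.3, no arm effect | about 63% to 93% | about 5% |
| Arms move +0.25 and −0.25 (gap 0.5) | about 4% to 5% | 98% |
| One arm flat, the other falls by 0.5 (gap 0.5) | about 79% | as above, since the 24 h gap is the same |

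The Monte Carlo standard error near 63% is √(0.63 × 0.37 / 1500) = 0.012, so differences of a point or two between runs are noise.

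A second set of 2,000 runs per scenario used the same SDs and larger changes (0.3 at 12 h, 0.5 at 24 h):
- No change in either arm: pooled Friedman 5.0%.
- Same trend in both arms, no arm effect: pooled Friedman 100%. Mann-Whitney on each patient's log change from 0 to 24 h: 5.1%.
- Opposite trends: pooled Friedman 3.5%. Mann-Whitney on change: 100%.

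The Friedman rejection rate follows the average time trend over all patients. It is high without a drug effect when the trend is shared, and it falls to the nominal level with a drug effect when the two trends cancel.

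**The case against.** The strongest reply is that the endpoint definition contains its own remedy. Change from enrolment to one named time is a single value per patient, hence independent across patients. The rule for non-correlated data would send it to Mann-Whitney, a valid arm test, and Friedman would then only describe trajectories within patients. This reading is possible, but the article does not state it. The Friedman sentence sits in the paragraph that poses the between-arm biomarker question, and nothing says that serial values will be reduced to change scores or which test serves which question. What stands is that a reader should not infer that no test named in the article could compare the arms.

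The reply is also right on the simulation figures. The 4% to 5% arises only when the arms move equally in opposite directions, so it is not typical of a 0.5 divergence. Running Friedman separately in each arm gives significance in one arm only in about 45% to 50% of trials under a shared fall of 0.2 to 0.3, but about 3% under a shared fall of 0.5. The article does not say the test will be run by arm, so no weight is placed on this.

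A reader might extend the criticism to repeated measures ANOVA. The documents do not support that: the method can carry arm and arm-by-time terms, and preferring a mixed model there is a matter of choice. Nor is the handling of incomplete sample series a finding, since a condensed article commonly leaves that to the full protocol or analysis plan.

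An unseen analysis plan does not dispose of the core point. The article names a method, and that method does not fit the question it is given.

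**Conclusion.** The point holds for the Friedman sentence and the tertiary analysis only. As written, the test assigned to non-normal correlated biomarkers has no treatment term, so its p-value cannot be attributed to furosemide. That conclusion follows from the form of the statistic alone. The rejection rates show the consequence under assumed variances and time courses and would change with other values. The 79% when only one arm changes does not rescue the test, because a shared trend without any drug effect gives similar rates.

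How many of the seven markers are affected is unknown, since the article does not say which are expected to be non-normal. A reader might infer that the trial's main conclusions are at risk. They are not: the primary outcome and the categorical secondary outcomes use Fisher's exact test, the other secondary analyses do not rely on Friedman, and the sample size rests on the primary outcome. The receiver operating characteristic analyses of the biomarkers are also untouched. This should be corrected, as a tertiary matter.

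**What to change.** Replace only the Friedman sentence with a between-arm method, chosen in advance from:

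- a mixed model on log-transformed values over the scheduled samples, with arm, time, arm-by-time, enrolment value and sepsis stratum (the randomization stratum), reporting the arm ratio with a 95% confidence interval at 12 h and 24 h; or
- a baseline-adjusted rank comparison, or Mann-Whitney on per-patient change, between arms at 12 h and at 24 h.

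Keep the values at start of RRT, renal recovery and ICU discharge as a separate between-arm comparison or description. The plan specifies them, and they do not fall at a common time, so they should be neither folded into the scheduled times nor dropped. Add a clause saying that the repeated measures ANOVA includes the arm factor and its interaction with time.

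The cost is a few lines of analysis text and standard software, with no new data and no change to sample size. The one small downside is that results may be reported as geometric-mean ratios.

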### Data Collection

Detailed clinical, procedure-related, physiologic and laboratory data will be collected. Blood and urine will be collected at baseline, 12 hours, 24 hours and daily thereafter until participants exits the study. Data will be collected on standardized CRFs developed by the EPICORE centre. Completed CRF will be returned to the EPICORE centre, entered into a central database, where data queries will be generated.

Clinical data captured will include demographics, co-morbidities and prescribed/current drug therapy. Details of admission diagnoses, surgical status, and dates of hospital and ICU admission will be recorded. Detailed data will be recorded on date of enrollment (i.e. fulfilling criteria for early AKI). This will include details of interventions (i.e. mechanical ventilation, vasoactive drugs, fluid therapy), hemodynamics (i.e. blood pressure, heart rate, central venous pressure), and acute physiology (i.e. components of severity of illness scores, urine output, fluid balance, secondary non-kidney organ dysfunction). During the trial, data will be collected daily on urine output, fluid balance, electrolytes, acid-base status, serum creatinine and urea. Collected blood and urine samples will be stored for batched analysis of kidney-injury specific biomarkers, including: serum and urine cystatin C, serum and urine neutrophil gelatinase-associated lipocalin (NGAL), urine interleukin-18 (IL-18); urine kidney injury molecule-1 (KIM-1), and urine L-type fatty acid binding protein (L-FABP).

Data will be collected each day on whether the primary endpoint (progression of AKI) has occurred, for evidence of any secondary endpoints and for criteria for trial discontinuation.

Finally, any study protocol violations will be recorded. The adjudication of protocol violations will be determined by a study investigator blinded to the treatment allocation.

All enrolled patients will be followed to determine the duration of AKI, continued need for RRT, renal recovery and mortality until death or discharge from hospital and at 30, 60 and 90-days after randomization.

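### ROC curves and 2 x 2 tables alone cannot show whether a biomarker adds anything to creatinine and urine output, which themselves define progression

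*Protocol article*

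**What the plan says.** Under Objectives, the third aim of the protocol article concerns "the tertiary endpoint of differences, trajectory and prognostic value of novel serum and urine biomarkers for AKI". The last paragraph of Statistical Analysis gives the method. It takes both the level of each marker and its change from enrolment, considers two outcomes (AKI progression and RRT), and states that performance against them "will be evaluated by 2 x 2 tables and construction of receiver operator characteristic curves". No reference model with routine measures is named there. The only regression named in the section is logistic or linear adjustment for baseline imbalance between the arms, which serves a different purpose.

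Three other places bear on the point:

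- **Operational Definitions, AKI, and Sample Size Estimation:** progression is movement from RIFLE Risk to Injury or Failure. Each class is set by a creatinine or a urine-output limit.
- **Operational Definitions, RRT:** the criteria for starting RRT include low urine output and raised urea, so this second outcome also overlaps with routine measures.
- **Data Collection:** seven assays are planned (serum and urine cystatin C, serum and urine NGAL, and urine IL-18, KIM-1 and L-FABP). Sampling is described as "Blood and urine will be collected at baseline, 12 hours, 24 hours and daily thereafter". Routine measures are also available: "During the trial, data will be collected daily on urine output, fluid balance, electrolytes, acid-base status, serum creatinine and urea".

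**The concern.** A patient enrolled with creatinine just below twice baseline, or with nearly 12 hours of low urine output, is close to being classed as progressed whatever any novel marker shows. A marker that rises with creatinine will therefore predict progression. Its ROC curve will look good even if a clinician who already has the creatinine and the urine chart learns nothing from it. A marker that picks up injury before creatinine moves may have a similar curve. The stated method gives the two the same kind of result.

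This matters for how the result is used. The Discussion says that the trial may help to design a phase III trial. A marker carried forward because of its stand-alone curve could prove redundant once creatinine and urine output are taken into account.

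**Working it through.** **The plan's own figure.** The article gives no figure for the biomarker analysis. Its sample size supplies N and the event rate, so I checked that first. Inputs from Sample Size Estimation are 60% versus 40%, power 80% and alpha 0.05. The test is two-sided (Statistical Analysis).

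- n = [1.960 × √(2 × 0.5 × 0.5) + 0.842 × √(0.24 + 0.24)]² / 0.20² = (1.386 + 0.583)² / 0.04 = 96.9 per arm.
- With continuity correction: (96.9 / 4) × [1 + √(1 + 4 / (96.9 × 0.20))]² = 106.7, so 107 per arm and 214 in total. This matches the article.
- The average progression rate is (60% + 40%) / 2 = 50%, or 108 of the final 216.

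**A fully redundant marker.** Assumptions, none of them in the documents:

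- Creatinine is normally distributed in progressors and non-progressors, with means d apart and AUC A, so d = √2 × z(A).
- The marker is ρ × creatinine + √(1 − ρ²) × independent noise. It carries nothing beyond creatinine.

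The marker's own AUC is then Φ(ρ × z(A)). For example, A = 0.70 and ρ = 0.5 give Φ(0.5 × 0.524) = Φ(0.262) = 0.603. A = 0.80 and ρ = 0.9 give Φ(0.9 × 0.842) = Φ(0.757) = 0.776. A test of AUC = 0.5 with 108 and 108 patients has null standard error √(217 / (12 × 108 × 108)) = 0.0394. Any AUC above 0.5 + 1.96 × 0.0394 = 0.577 is therefore significant.

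Simulation with 1,500 trials per row agrees with the formula:

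| Creatinine AUC | ρ | Mean marker AUC | Trials with p < 0.05 | True added value |
|---|---|---|---|---|
| 0.70 | 0.5 | 0.603 | 74% | 0 |
| 0.70 | 0.7 | 0.643 | 95% | 0 |
| 0.70 | 0.9 | 0.682 | 99.8% | 0 |
| 0.75 | 0.5 | 0.633 | 93% | 0 |
| 0.75 | 0.7 | 0.681 | 99.8% | 0 |
| 0.75 | 0.9 | 0.729 | 100% | 0 |
| 0.80 | 0.5 | 0.662 | 99% | 0 |
| 0.80 | 0.7 | 0.722 | 100% | 0 |
| 0.80 | 0.9 | 0.776 | 100% | 0 |

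These AUCs are not biased. They are correct answers to the crude question. A likelihood-ratio test of the same marker, given creatinine, would reject at about the nominal 5%.

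**If a 2 x 2 cut-off were chosen on the same data.** This part is conditional, because the article does not say how cut-offs arise. The table shows J = sensitivity + specificity − 1 at the best cut-off, minus the true J at that cut-off. It uses N = 216 and 3,000 simulated trials per cell, with higher values always read as positive. The 25% and 10% event rates are assumed, with RRT in mind.

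| Event rate | AUC 0.5 | AUC 0.6 | AUC 0.7 | AUC 0.8 |
|---|---|---|---|---|
| 50% | 0.079 | 0.071 | 0.060 | 0.052 |
| 25% | 0.094 | 0.082 | 0.071 | 0.061 |
| 10% | 0.133 | 0.122 | 0.113 | 0.096 |

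At AUC 0.7 and a 50% event rate, sensitivity reads 0.66 against a true 0.63, and specificity 0.67 against 0.65. At a 10% event rate, sensitivity reads 0.72 against 0.61. With a cut-off fixed independently of these patients, this optimism is zero.

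**The case against.** The strongest reply is that the stated aim is prognostic value, not added value. A stand-alone ROC curve does estimate prognostic discrimination, and a marker that tracks creatinine and predicts progression is a genuine predictor. This stands: reporting such a marker as a predictor is not an error. What remains is that crude discrimination is hard to interpret when the outcome is built from the routine measures themselves.

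The second reply is that the article is condensed and the SAP is not shown, so a reference model and cut-off rules may exist there. This largely disposes of the cut-off question. It weighs less against the reference model, because the article does name its method and that method cannot answer the question of added value.

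A reader might go further and infer that cut-offs will be read off the trial's own ROC curves, so that accuracy will be overstated. The documents do not support that. Statistical Analysis lists the tables and the curves side by side and names no source for cut-offs. The AUC of a marker named in advance needs no cut-off and is not inflated for want of one. Nor does the text say that each assay will be judged only on its own. Picking the best of seven markers is a multiplicity question. Calculations that treat the seven as independent do not fit a panel with serum and urine versions of the same two proteins.

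A final caution concerns the remedy. The infusion is titrated to urine output (Study Intervention), and creatinine and urine output define the endpoint. Adjusting for their post-enrolment values is therefore awkward.

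**Conclusion.** The concern holds in a limited form. The stated analysis estimates crude discrimination validly. It cannot show whether a marker adds to creatinine and urine output, and for an endpoint defined by those two measures that is what a reader will want to know. Under the assumptions above, a marker with no added value shows an AUC of about 0.60 to 0.78 and is significant in 74% to 100% of trials. The size depends on the assumed creatinine AUC, the assumed correlation and the normal model, none of which the documents give.

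It is not established that sensitivity and specificity will be overstated. That follows only if cut-offs are tuned on the same patients. J would then be overstated by about 0.05 to 0.08 at a 50% event rate and by about 0.10 to 0.13 at an assumed 10%. The primary analysis, sample size and safety assessment are untouched. This is a minor, optional improvement to a tertiary analysis.

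**What to change.** Keep the ROC curves and add wording such as:

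> For progression and for RRT, a logistic reference model will contain enrolment creatinine relative to baseline, enrolment urine output, treatment arm and sepsis stratum. It will be fitted in patients who have not yet had the event when the marker sample is taken. Each marker's added value will be reported by likelihood-ratio test and by change in AUC with 95% confidence interval. Where a 2 x 2 cut-off is chosen from the trial's own data, sensitivity and specificity will be corrected for optimism by bootstrap.

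Enrolment values avoid conditioning on what the infusion is titrated to change. The price is that, for the 12- and 24-hour samples, the model asks whether the marker adds to what was known at enrolment, not to creatinine at the same hour.

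Fixing cut-offs before unblinding would not be enough. A pooled ROC curve needs only marker and outcome, so a cut-off could be tuned on these patients while allocation is still masked.

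The cost is a few lines of analysis and programming. The routine measures are already collected and sepsis is the randomization stratum. Marker performance will look less favourable. For RRT the model may be thin: at an assumed 10% event rate there would be 216 × 0.10 ≈ 22 events for five coefficients (four covariates and the marker), about four each, so intervals will be wide.

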### Data Safety and Monitoring

The trial will have a data safety and monitoring committee (DSMC) that will consist of four members. Three members will constitute a quorum. The membership consists of persons independent of the Principal Investigator who have no financial, scientific, or other conflict of interest with the trial. Current or past collaborators of Principal Investigator are not eligible to serve on the DSMC. Members of the DSMC will have clinical/content expertise in acute kidney injury; clinical trial methodology and/or biostatistics. The DSMC will meet twice per year during the trial.

### Ethical Considerations

The study has been reviewed and approved by the Health Research Ethics Board at the University of Alberta (File # 7362) (Additional File 1).

### Potential Challenges with the Trial

Research in patients with AKI has been traditionally challenging due to lack of a standardized definition or classification scheme for AKI. In order to address this issue, and optimize the potential generalizability, we have incorporated the RIFLE definition/classification system for AKI[42]. This consensus definition has now been validated and its clinical use is strengthened by its objectivity, simplicity and by the incorporation of a system to categorize the changes in severity of AKI over time.

The development of acute pulmonary edema in an ICU patient with AKI was identified in our survey as an indication for urgent furosemide or RRT and as such a potential barrier to compliance with our trial[20]. We have addressed this in our protocol by including a provision for the urgent use of furosemide in any enrolled patient with pulmonary edema at the discretion of the consultant ICU physician. Similarly, RRT can be initiated at any time.

Another potential issue with the protocol was the handling of an excess diuresis following initiation of the study drug. To address this, we have incorporated into our study algorithm provisions to temporarily discontinue the study drug in the event of an excess diuresis. Similarly, electrolyte abnormalities, in particular low magnesium and potassium, are common with use of furosemide. This issue is addressed by our ICU having standardized protocols for the replacement of both of these electrolytes in the event they are significantly low.

We do not anticipate any losses to follow-up during the study intervention. This is due to our primary outcome, progression in severity of kidney injury in AKI, being measured while the patient is admitted to ICU. A situation may arise where a patient is randomized and allocated as non-septic but subsequently develops sepsis during the trial. We will address this potential issue by analyzing all these patients according to their initial allocated group.

